#### **Recruitment {15}**

Participants will be recruited through local non-government agencies and schools in Herat and Kabul.

#### **Assignment of interventions: allocation**

#### **Sequence generation {16a}**

After eligibility is confirmed and baseline data collected, participants will be randomly assigned in a 2:1 ratio to METRA or TAU ([CHANGE 5: Change in random assignment ratio approach due to resource and ethical reasons](#)). We have adopted an unequal randomization approach for resource and ethical reasons to maximize the number of participants in the treatment arm. This decision was made because following the change of government, there was increased insecurity and most international agencies withdrew from Afghanistan. Thus, there are now very few youth health interventions available that can be considered TAU. This unequal randomization approach has been employed in previous trauma-focused RCTs (including those conducted in LMICS) (Bass et al., 2016; Rae Olmsted et al., 2020) and the decision should not impact power for our statistical tests nor changed the scientific rigor of the study (Torgerson & Torgerson, 2008).

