#### **Sample size {14}**

A priori power analysis was undertaken using G\*Power for depression and PTSD outcomes to detect a small to moderate interaction effect ( $f=0.15$ ) [18,33] between group (intervention, control) and time (pre-test, post-test) at an alpha-level of 0.05. A sample size of 90 participants would achieve power  $>0.80$ . The sample size estimate was re-adjusted to allow for attrition and we aim to recruit  $>100$  participants.

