**Statistical methods****Statistical methods for primary and secondary outcomes {20a}**

All primary analyses will be on intent-to-treat principle, with all randomized participants analyzed in their allocation condition.

Objective 1 will be examined using linear mixed effects models with intervention type, time, and intervention by time interaction as fixed factors (CHANGE 6: This was changed to generalized estimating equations following reviewer feedback. However, the results were the similar when using linear mixed effects models). Repeated assessments of individuals will be modelled as random intercept. Of primary interest will be the intervention by time interaction, which will compare the levels of change over time in outcomes of the METRA and TAU groups. Levels of significance will be set at  $\alpha < .05$  and hypothesis tests will be 2-sided. Objective 2: Thematic analysis of qualitative data (Atkins et al., 2017; Braun & Clark, 2006; Marks & Yardley, 2004) will assess feasibility and appropriateness.

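### The statement that 2:1 allocation leaves power unaffected is wrong at a fixed total sample size, and the sample-size section was not updated for the new ratio

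*Supplement*

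**What the plan says.** Both passages stand in Version 2 of the protocol (September 2021).

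- **Sample size {14}.** "A priori power analysis was undertaken using G\*Power for depression and PTSD outcomes", for a Cohen f of 0.15 on the interaction "between group (intervention, control) and time (pre-test, post-test"), "at an alpha-level of 0.05". The result is given as "A sample size of 90 participants would achieve power" above 0.80. The only later adjustment is for dropout: "The sample size estimate was re-adjusted to allow for attrition and we aim to recruit" more than 100. No pre-post correlation, allocation ratio or attrition rate is given.
- **Sequence generation {16a}.** Allocation becomes 2:1, METRA to TAU, for resource and ethical reasons. With a textbook on trial design as its source, the section adds that "the decision should not impact power for our statistical tests nor changed the scientific rigor of the study".

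The effect size, the 90 and the power are the same as in Version 1, which mentioned no 2:1 ratio.

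**The concern.** With the total fixed, moving from equal to unequal groups always loses precision on a two-arm contrast. Power is preserved only if the total rises to compensate. The sample-size section raises the total for attrition and does not mention the ratio, so its figure appears to describe an equal-allocation trial rather than the one Version 2 sets out.

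A reader who takes the two sections together would conclude that 90 evaluable participants split 60/30 give power above 0.80, with everyone beyond 90 available to absorb losses. If that is not so, a null result on PTSD or depression symptoms would be read with more confidence than the design supports.

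**Working it through.** **Inputs from the protocol.** f = 0.15; 2 groups; m = 2 time points; alpha 0.05, with {20a} stating that "hypothesis tests will be 2-sided"; N = 90; stated power above 0.80; recruitment above 100; allocation 2:1.

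**Assumptions, not in the protocol.** Pre-post correlation ρ = 0.5 (the G*Power default), varied in step 5. Equal groups in the calculation as stated.

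**Formula.** Noncentral F test of the group-by-time interaction, with 1 and N − 2 degrees of freedom and noncentrality

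λ = [f² × N × m / (1 − ρ)] × 4p(1 − p),

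where p is the proportion allocated to METRA. The last factor is 1 at 1:1 and 4 × (2/3) × (1/3) = 8/9 at 2:1.

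**Step 1: the plan's own figure.** At 1:1 with ρ = 0.5, λ = 0.0225 × 90 × 2 / 0.5 = 8.1 and power is 0.804. At N = 89 it is 0.799. So 90 is exactly the smallest total above 0.80 under these assumptions, which is good evidence, though not proof, that they were the ones used.

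**Step 2: the loss that needs no correlation.** Information on the contrast is proportional to n₁n₂/N.

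- 45/45: 45 × 45 / 90 = 22.5
- 60/30: 60 × 30 / 90 = 20.0

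The loss is 1 − 20.0/22.5 = 11%. Ninety participants at 2:1 are worth 90 × 8/9 = 80 at 1:1. Neither figure involves ρ.

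**Step 3: power at 2:1 with ρ = 0.5.** λ = 8.1 × 8/9 = 7.2, and power at N = 90 is 0.756. As a cross-check, f = 0.15 with ρ = 0.5 corresponds to a difference in change of 0.6 SD (0.36 × 22.5 = 8.1; 0.36 × 20.0 = 7.2). The normal approximation on that scale gives 0.812 at 45/45 and 0.765 at 60/30, a drop of the same size.

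**Step 4: total needed at 2:1 with ρ = 0.5.**

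| Evaluable N | Power at 1:1 | Power at 2:1 |
|---|---|---|
| 90 | 0.804 | 0.756 |
| 100 | 0.844 | 0.7997 |
| 101 | 0.848 | 0.804 |
| 102 (68/34 at 2:1) | 0.851 | 0.808 |

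The inflation that 2:1 requires is 90 × 9/8 = 101.25. This is nearly the whole step from 90 to the recruitment floor. With 101 recruited and 90 analysed (10.9% loss), power is 0.804 at 1:1 and 0.756 at 2:1. With an assumed 10% loss, 102 evaluable would take 102/0.9, or about 114 recruited.

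**Step 5: sensitivity to ρ at N = 90.**

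| ρ | Power at 1:1 | Power at 2:1 |
|---|---|---|
| 0.4 | 0.729 | 0.678 |
| 0.5 | 0.804 | 0.756 |
| 0.6 | 0.882 | 0.843 |
| 0.7 | 0.953 | 0.929 |

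At 2:1, λ = 3.6/(1 − ρ). Power reaches 0.80 when λ is about 8.0, that is, at ρ of about 0.55. Power is lower at 2:1 than at 1:1 in every row.

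**The case against.** The strongest reply is that the protocol states no correlation and claims only power above 0.80, without saying that 90 is the minimum. Equal groups with any ρ of about 0.5 or more satisfy that sentence, and so does 2:1 with 90 participants once ρ is about 0.55. A reader might therefore infer too much in saying that the trial's power is below 0.80. The documents do not establish that; 0.756 is conditional on ρ = 0.5. This part of the reply stands.

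Second, a reader might infer that the attrition allowance has been used up. The target is an open floor with no attrition rate attached, and recruiting about 114 with 10% loss would fit both the text and 80% power. What can be said is that, if ρ = 0.5, the floor itself leaves no margin. The mention of increased movement in the trial-design section does not settle the matter either. It is given as the reason for shortening follow-up to 3 months, whereas the power calculation concerns pre-test to post-test.

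Third, the calculation treats each dropout as contributing nothing to a two-time-point test. The planned analysis uses repeated measures over four assessments on an intent-to-treat basis, so participants with partial data can contribute. The power figures after attrition therefore do not describe the planned model. Nor do they allow for METRA being delivered in groups of 6 to 8.

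Finally, it could be said that more than 100 at 2:1 roughly matches 90 at 1:1, so power is preserved after all. That would hold if the increase had been made for the ratio. The sample-size section assigns it to attrition, and the same participants cannot serve both purposes.

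None of this rescues the clause itself. At a fixed total, 2:1 lowers power at every correlation.

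**Conclusion.** The statement in {16a} is wrong as written, and {14} was not revised for the new ratio. The part that needs no assumption about correlation is the 11% loss of effective sample size. The loss of power, from 0.804 to 0.756 at 90 evaluable participants, and the need for about 101 to 102 evaluable to reach 0.80, both rest on ρ = 0.5 and on the pre/post test that the plan itself used for sizing.

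The loss is modest, about 5 percentage points. It introduces no bias and no inflation of type I error, and it does not undermine the choice of 2:1. It should still be corrected, because a stated power property does not match the design. Version 2 already carries after-the-fact notes (for example, that results were similar under either model), so the correction mainly sets the record straight for readers of the results.

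**What to change.** 1. In {16a}, delete the clause saying that 2:1 does not affect power. The resource and ethical reasons can stay as they are.
2. In {14}, state the correlation and allocation ratio used in the G*Power run and restate the figure for 2:1. If the correlation was 0.5, suitable wording would be:

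> For the pre/post interaction test, assuming a correlation of 0.5, 90 evaluable participants at 2:1 (60/30) give about 76% power and about 102 give 80%. This figure is for the two-time-point test and does not account for group delivery or the four-assessment model.

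If another correlation was used, the same sentence should carry that value and the power it gives.

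The cost is two or three sentences of protocol text and, at a correlation of 0.5, a slightly less favourable stated power. No extra enrolment and no change to the allocation or analysis is needed.

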### **Concealment mechanism {16b}**

We will use consecutively numbered sealed opaque envelopes to conceal the allocation.

### **Implementation {16c}**

The research team will oversee generation of the allocation sequence, participant enrollment, and assigning participants to interventions.

### **Assignment of interventions: Blinding**

#### **Who will be blinded {17a}**

Outcome assessors will be blind to hypotheses and group allocation. Group facilitators will be blind to hypotheses.

#### **Procedure for unblinding if needed {17b}**

Not applicable

### **Data collection and management**

#### **Plans for assessment and collection of outcomes {18a}**

Data will be collected at; 1) baseline, 2) post-Module 1, 3) post-Module 2, and 4) ~~6-month~~ 3-month follow-up. Assessments will be conducted by independent raters who have no therapeutic relationship with participants and are blind to condition. All assessors will be trained and supervised in assessment procedures. All questionnaires have good reliability and validity and have been previously used cross-culturally.

#### **Plans to promote participant retention and complete follow-up {18b}**

Participants will be contacted using a variety of media, including phone, email and social media to promote retention and follow-up completion.

**Data management {19}**

Data will be coded, entered and stored in Kabul and Herat on password protected computer systems. Anonymized data will be shared amongst the research team.

**Confidentiality {27}**

Personal information about potential and enrolled participants will only be collected, shared, maintained and monitored by the research teams at each site. De-identified data will be shared between the team.

**Plans for collection, laboratory evaluation and storage of biological specimens for genetic or molecular analysis in this trial/future use {33}**

N/A

**Statistical methods****Statistical methods for primary and secondary outcomes {20a}**

All primary analyses will be on intent-to-treat principle, with all randomized participants analyzed in their allocation condition.

Objective 1 will be examined using linear mixed effects models with intervention type, time, and intervention by time interaction as fixed factors (CHANGE 6: This was changed to generalized estimating equations following reviewer feedback. However, the results were the similar when using linear mixed effects models). Repeated assessments of individuals will be modelled as random intercept. Of primary interest will be the intervention by time interaction, which will compare the levels of change over time in outcomes of the METRA and TAU groups. Levels of significance will be set at  $\alpha < .05$  and hypothesis tests will be 2-sided. Objective 2: Thematic analysis of qualitative data (Atkins et al., 2017; Braun & Clark, 2006; Marks & Yardley, 2004) will assess feasibility and appropriateness.

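### The primary model is a change-score comparison: it is unbiased, but makes inefficient use of a baseline measured before randomisation, and the size of the loss depends on quantities the plan does not state

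*Supplement*

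**What the plan says.** All references are to protocol version 2. Section {20a} specifies the model: "Objective 1 will be examined using linear mixed effects models with intervention type, time, and intervention by time interaction as fixed factors". The repeated measures are handled as follows: "Repeated assessments of individuals will be modelled as random intercept". The interaction is the effect of primary interest, and its purpose is to "compare the levels of change over time in outcomes of the METRA and TAU groups". An inserted note on the estimator says: "This was changed to generalized estimating equations following reviewer feedback". The note leaves the fixed terms as they were and adds that the two estimators gave similar results.

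Section {18a} makes baseline the first of four assessments: baseline, post-Module 1, post-Module 2 and a 3-month follow-up. Section {16a} fixes the order of events: "After eligibility is confirmed and baseline data collected, participants will be randomly assigned in a 2:1 ratio to METRA or TAU". Section {14} gives the sample size: 90 participants for power above 0.80 to detect an interaction of f = 0.15 between two groups and two times at alpha 0.05, raised to more than 100 for attrition. Section {10} admits participants who score above 30 on the PTSD scale and/or above 12 on the depression scale. The plan nowhere enters the baseline score as a covariate or constrains the arms to a common baseline mean.

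**The concern.** With baseline as a response visit, the arm main effect estimates a baseline difference between the arms. Randomisation comes after the baseline assessment, so the true difference is zero, and estimating it uses up information. The interaction then subtracts the whole observed baseline difference, whatever the correlation between baseline and follow-up. An adjusted analysis subtracts only the share that baseline predicts.

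Precision is at stake, not validity. It matters here because the trial is small and allocates 2:1. At 90 participants the control arm has 30, and with unequal arms the same total gives a contrast with 12.5% more variance. Chance baseline imbalance is also more likely in small arms, and the planned contrast corrects for it by a fixed amount, not by the amount the data support.

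**Working it through.** **Inputs.** From the protocol: f = 0.15, two groups by two times, alpha 0.05 two-sided, N = 90 ({14}, {20a}); 2:1 allocation ({16a}); four assessments ({18a}). Not stated, and therefore assumed over a range: rho, the correlation between baseline and a follow-up visit, and k, the baseline SD divided by the follow-up SD.

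**1. Reproduce the plan's figure.** For the group-by-time interaction with m = 2 times and equal variances, lambda = f²·N·m/(1−rho), on 1 and N−2 degrees of freedom. At rho = 0.5, lambda = 0.0225 × 90 × 2/0.5 = 8.1 and power is 0.804. N = 90 is the smallest even total that reaches 0.80. Other correlations do not return 90: rho 0.3 gives 126, 0.4 gives 108, 0.6 gives 72 and 0.7 gives 56. So rho = 0.5 is inferred from the stated N, not taken from the text.

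In a 2×2 layout with equal groups, the interaction cell effects are ±delta/4, so delta = 4 × 0.15 = 0.60 SD difference in change. As a check, 0.6²/[2(1−0.5)(1/45+1/45)] = 0.36/0.0444 = 8.1.

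**2. Confirm what the model estimates.** On one simulated complete data set (60:30, four categorical times), the random-intercept mixed model, the exchangeable GEE and the plain difference in mean change all gave 0.5713. The change of estimator does not alter the contrast.

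**3. Variance at one visit**, in units of follow-up variance times (1/n1+1/n2):
- Change score: k²+1−2·rho·k
- Baseline-adjusted, with the slope estimated from the data: 1−rho²
- The first minus the second is (k−rho)², which is never negative. In large samples, such adjustment therefore cannot raise the variance.

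| | rho 0.3 | rho 0.5 | rho 0.7 |
|---|---|---|---|
| k = 1: ratio | 0.91/1.40 | 0.75/1.00 | 0.51/0.60 |
| k = 1: cut | 35% | 25% | 15% |
| k = 0.8: ratio | 0.91/1.16 | 0.75/0.84 | 0.51/0.52 |
| k = 0.8: cut | 22% | 11% | 2% |
| k = 0.7: ratio | 0.91/1.07 | 0.75/0.79 | 0.51/0.51 |
| k = 0.7: cut | 15% | 5% | 0% |

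In 20,000 simulated trials at rho = 0.5 and k = 1, the variance was 0.0511 for the change score, 0.0386 with baseline as covariate (24.5% lower) and 0.0381 with a common baseline mean (25.5% lower).

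**4. Illustrative power**, for one visit, 60/30 independent participants and a 0.6 SD difference, where 1/60+1/30 = 0.05:
- k = 1, rho = 0.5, change score: lambda = 0.36/(1.00 × 0.05) = 7.2, power 0.756
- k = 1, rho = 0.5, adjusted: lambda = 0.36/(0.75 × 0.05) = 9.6, power 0.865
- k = 0.8, rho = 0.5, change score: lambda = 0.36/(0.84 × 0.05) = 8.57, power 0.825; adjusted, 0.865 as before

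With k = 1, power goes from 0.611 to 0.794 at rho 0.3 and from 0.929 to 0.960 at rho 0.7.

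**5. Effect of entry selection.** Take normal scores with an unselected correlation of 0.5 and equal SDs, and admit the upper half on the same scale. Baseline variance becomes 1−2/π = 0.363 and follow-up variance 0.75+0.25 × 0.363 = 0.841. Then k = 0.603/0.917 = 0.66 and rho = 0.5 × 0.603/0.917 = 0.33. The true ratio is 0.892/1.00, a cut of 11%. The equal-variance formula at rho = 0.33 would suggest about 34%. A milder rule, passing on either of two scales correlated 0.5 with both cut at the mean, gives 19%.

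**The case against.** The change contrast is unbiased, is the quantity the sample size was built on, and contradicts nothing else in the plan. On that view this is a preference about efficiency. That stands as to kind: nothing here makes the planned estimate wrong, and a reader who inferred bias would go too far.

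A reader might also infer a flat 25% saving. The documents do not support that. The figure needs rho = 0.5, which is only back-solved from N = 90, and equal variances, which the entry cut-offs may break. Nor should one argue that selection lowers rho and so enlarges the gain: step 5 shows that the accompanying fall in baseline variance can reverse this.

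It is tempting as well to say that adjustment more than offsets the cost of 2:1 allocation. It does at k = 1 and rho = 0.5, where 1.125 × 0.75 = 0.84. With an 11% cut it only breaks even, since 1.125 × 0.89 = 1.00.

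The power figures are not the power of this trial's primary test. They concern one of three post-baseline visits and treat participants as independent, although METRA is delivered in groups of 6 to 8. Any within-group correlation would lower both members of each pair.

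Finally, the note in {20a} compares results from two estimators, so outcome data had been analysed when it was written. Replacing the primary model now would be a post hoc choice. That limits how the fix should be presented, but does not remove the case for it.

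**Conclusion.** The point holds as one of efficiency. Under either estimator the plan compares change scores and leaves unused the knowledge that the arms share a baseline mean. The exact identity assumes categorical time, whose coding the plan does not state, and complete data.

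The direction of the gain does not depend on rho or k, provided the adjustment slope is estimated from the data. The size does. Over rho 0.3 to 0.7, the per-visit variance cut is 35% to 15% with equal variances and 22% to 2% at k = 0.8. It vanishes where k equals rho. The plan's own N = 90 points to rho = 0.5, hence 25% if variances are equal and 11% if k = 0.8. The change is worth making because it needs no further data and the control arm is small.

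**What to change.** In {20a}, for both primary scales and all secondary scales, state that time is categorical and replace the mean structure with a common baseline mean for the two arms plus arm-by-visit terms at the three post-baseline visits. This can be fitted as a mixed model or by GEE, and it keeps every randomised participant with a baseline score.

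The covariance must be stated too. With a random intercept or exchangeable working correlation, the baseline slope is fixed at the common correlation instead of being estimated at each visit. With an independence working correlation, there is no baseline adjustment at all. If k differs from 1, a fixed slope can lose the gain: at k = rho = 0.7, a slope of 0.7 gives variance 1+0.49 × 0.49−2 × 0.7 × 0.7 × 0.7 = 0.554, against 0.51 for the change score. An unstructured covariance with visit-specific variances avoids this.

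The alternative is to model post-baseline scores with baseline and baseline-by-visit as covariates, which suits GEE. It drops anyone with no post-baseline score, so its fit with the intention-to-treat statement in {20a} should be addressed.

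The cost is analysis wording and a re-run, with no new data and no burden on participants. Because results had been seen, label the new model as a post hoc change or report it beside the planned one, and give the observed rho and k so that readers can judge the gain.

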### **Intervention description {11a}**

METRA: Module 1: Memory specificity training ([name] et al., 2018; Moradi et al., 2014; Neshat-Doost et al., 2013; Raes et al., 2009; Martens et al., 2019) is a manualized training delivered over five 60-minute sessions to groups of 6-8 adolescents. MEST aims to enhance memory specificity through practice. Session 1 provides psycho-education about mental health and memory.

Participants practice recalling memories in response to positive and neutral cues, with support from the group facilitator. Attention is paid to the contextual, spatio-temporal and sensory-perceptual details of the memories (Raes et al., 2009). Participants' responses are discussed in the group. At the end of the session, homework exercises are introduced; for 10 cues (positive and neutral) participants need to generate a specific memory and are instructed to write down a 'specific memory of the day' every evening of the coming week (Raes et al., 2009). Session 2 starts with a brief summary of Session 1, the homework exercises are discussed and the Session then follows the same format as Session 1, with further practice focusing on recalling memories in response to positive and neutral cues. At the end of Session 2, the homework is explained; participants need to generate two different specific memories for 10 cues (positive and neutral) and write down two different 'specific memories of the day' every evening of the coming week (Raes et al., 2009). Session 3 is very similar to Session 2. However, in Session 3, participants also need to work with negative cues. The homework exercises are similar to those outlined in Session 2, but now also include negative cues. Session 4 involves further exercises using negative and ('counterpart') positive cues. It is also explained how overgeneral thinking can be addressed by recalling a single specific experience and examples are discussed to promote metacognitive awareness of when participants are starting to shift to unspecific thinking or more general retrieval (Raes et al., 2009). Session 5 includes further practice and a summary of Module 1. Module 1 focuses on everyday remembering.

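### METRA Module 1 is delivered in groups, but neither the primary analysis nor the sample size allows for delivery group; if outcomes correlate within groups, standard errors are too small

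*Supplement*

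**What the plan says.** All references are to protocol Version 2.

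- **Allocation** (Sequence generation {16a}): participants are assigned at random, 2:1, to METRA or TAU. Nothing suggests that clusters are assigned.
- **Delivery** (Intervention description {11a}): Module 1 "is a manualized training delivered over five 60-minute sessions to groups of 6-8 adolescents", and participants' responses are discussed in the group. No group size is given for Module 2, where the facilitator reads instructions and participants write.
- **Comparator** (Explanation for the choice of comparators {6b}): the content of TAU is left to local NGOs and will be documented. Whether it is individual or group care is not stated.
- **Analysis** (Statistical methods {20a}): "linear mixed effects models with intervention type, time, and intervention by time interaction as fixed factors". On dependence the section says only this: "Repeated assessments of individuals will be modelled as random intercept". A note in the same section records a change to GEE and says that results were similar under both methods. It names no cluster unit.
- **Sample size** ({14}): "A sample size of 90 participants would achieve power" above 0.80 for a group-by-time interaction of f = 0.15 with two groups and two times, "at an alpha-level of 0.05". The target is then raised to more than 100 for attrition. No ICC or design effect appears.

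No section names delivery group or facilitator as a random effect, a cluster unit or a sensitivity analysis.

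**The concern.** Adolescents who are randomised individually and then treated together share a facilitator, peers and session content. Their outcomes may move together for reasons unrelated to the average effect of METRA. This is a partially nested design, with grouping described in one arm and none described in the other. A model that knows only about repeated measures within a person treats different METRA participants as independent.

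Any positive within-group correlation then makes the reported standard error of the arm-by-time contrast too small. The error runs in one direction: intervals too narrow, too many false positives, and a power figure that is too high. It affects the main contrast on both primary outcomes, PTSD and depression symptoms.

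**Working it through.** **1. Inputs from the documents.** f = 0.15; two groups and two times; alpha 0.05, and "hypothesis tests will be 2-sided"; N = 90; recruitment target above 100; allocation 2:1; Module 1 groups of 6-8.

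**2. Inputs assumed.** Pre-post correlation ρ = 0.5; ICC of change within METRA groups 0, 0.02, 0.05, 0.10 and 0.15; group size m = 7; TAU participants independent; 102 analysed, split 68 to 34.

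**3. Reproducing N = 90.** For the within-between interaction in a repeated-measures ANOVA with 2 times, λ = f² × N × 2 / (1 − ρ) = 0.0225 × 90 × 2 / 0.5 = 8.1. With 1 and 88 degrees of freedom the power is 0.804. The stated figure is therefore reproduced with every participant independent, equal arms and ρ = 0.5. It depends on ρ: the required N would be 126 at ρ = 0.3 and 56 at ρ = 0.7.

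With equal arms λ = N × d² / 4, so d² = 4 × 8.1 / 90 = 0.36. The effect is thus a standardised difference in change of d = 0.6.

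**4. Reference power at 68 and 34, no clustering.** λ = 0.36 × (68 × 34 / 102) = 8.16, which gives power 0.81.

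**5. Adding grouping in METRA only.**

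- METRA design effect: DE = 1 + (m − 1) × ICC.
- Variance inflation of the arm difference: V = (DE/68 + 1/34) / (1/68 + 1/34). At 2:1 the METRA arm supplies one third of the variance, so V = 1 + (m − 1) × ICC / 3.
- True type I error of a nominal 5% test: 2 × [1 − Φ(1.96 / √V)].
- Power of a valid test: as in step 4, with λ = 8.16 / V.
- Effective METRA sample: 68 / DE.

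Results for m = 7:

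| ICC | DE | V | Reported SE / correct SE | Type I error | Power | Effective METRA n |
|---|---|---|---|---|---|---|
| 0 | 1.00 | 1.00 | 1.00 | 5.0% | 0.81 | 68 |
| 0.02 | 1.12 | 1.04 | 0.98 | 5.5% | 0.79 | 61 |
| 0.05 | 1.30 | 1.10 | 0.95 | 6.2% | 0.77 | 52 |
| 0.10 | 1.60 | 1.20 | 0.91 | 7.4% | 0.73 | 43 |
| 0.15 | 1.90 | 1.30 | 0.88 | 8.6% | 0.70 | 36 |

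Over group sizes 6 to 8 the type I error is 6.0-6.4% at ICC 0.05 and 7.0-7.8% at ICC 0.10.

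**6. Simulation check.** Change scores were simulated 40,000 times under no effect, with 68 METRA in groups of 7 and 34 TAU.

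- A pooled test that ignores group rejected in 4.9%, 6.0% and 7.4% of runs at ICC 0, 0.05 and 0.10, in line with the formula.
- A robust variance clustered on the participant, standing in for GEE, rejected in 5.7%, 6.9% and 8.2%. The 5.7% at ICC 0 is small-sample bias, so 0.7 to 0.9 points of the other figures are not due to grouping.
- A robust variance clustered on METRA group, with TAU as singletons and small-sample degrees of freedom, stayed between 4.8% and 5.1% over group sizes 6-8 and ICCs from 0 to 0.20.

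The simulation uses one change score per person, as the sample size does, and not the full four-visit model.

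**The case against.** The strongest reply is that nothing in the documents shows a positive ICC. At ICC 0 the planned analysis loses nothing through grouping, and at 0.02 to 0.05 the excess over 5% is about half a point to just over one point. Grouping is described in one arm only, and that arm carries a third of the variance. All of this stands. A reader might infer that the type I error definitely exceeds 5%; the documents do not support that, and the point has to be conditional.

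A reader might also infer that the METRA mean rests on about 10 groups instead of 68 adolescents. That would be true only at ICC 1. Over the range shown, the arm is worth between 61 and 36 independent participants.

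Two limits of the text also stand. Group size and group discussion are documented for Module 1 only; the background calls the approach group-based in general terms, which does not settle how Module 2 is run. And the format of TAU is unknown, so treating its participants as independent is an assumption.

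Two further replies do not help the plan. The move to GEE leaves the gap, because no group-level cluster is named and clustering on the participant does not remove the inflation. The note that both methods gave similar results is no reassurance on this point, because neither is described as including group.

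**Conclusion.** The omission is real and touches the primary contrast: the plan assumes zero correlation within METRA groups without saying so, although its own description has members discussing their responses together. If that correlation is positive, standard errors are too small. The size is modest to moderate, with true type I error from about 5.5% to 8.6% and a loss of about 2 to 11 points of power for ICCs from 0.02 to 0.15.

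The type I figures rest on the assumed ICC range, groups of about 7, a 68 to 34 split and ungrouped TAU. The power figures rest in addition on a pre-post correlation of 0.5 and on no attrition from 102. The documents neither support nor exclude any particular ICC in the range.

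**What to change.** - **Data:** record a METRA group identifier for each participant, and take from the TAU documentation whether TAU was given in groups.
- **Mixed model:** use a partially nested form, with a random METRA-group effect on the post-baseline visits and Satterthwaite or Kenward-Roger degrees of freedom.
- **GEE:** cluster the robust variance on METRA group, with a small-sample correction, and name the cluster unit in {20a}.
- **TAU:** treat each participant as a singleton unless the documentation shows group treatment; in that case use those groups.
- **Sample size {14}:** state that the power figure assumes independence, and give the assumed ICC range with its effect on power.

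The cost is one variable and one model term or cluster definition, slightly wider intervals and a less favourable power statement. With about 10 METRA groups (68 / 7) the group variance will be estimated imprecisely, which is why the small-sample correction is needed. The {20a} note reports results, so analyses have already been run; if group membership was not kept, it would have to be reconstructed from session records, or the limitation stated.
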